**Methods and analysis:**

The CORE-VNS study is an international, multicentre, prospective, observational, all-comers, post-market registry. People with DRE receiving VNS Therapy for the first time as well as people being reimplanted with VNS Therapy are eligible. Participants have a baseline visit (prior to device implant). They will be followed for a minimum of 36 months and a maximum of 60 months after implant. Analysis endpoints include seizure frequency (average number of events per month), seizure severity (individual-rated categorical outcome including very mild, mild, moderate, severe or very severe) as well as non-seizure outcomes such as adverse events, use of antiseizure medications, use of other non-pharmacological therapies, quality of life, validated measures of quality of sleep (Pittsburgh Sleep Quality Index or Children’s Sleep Habit Questionnaire) and healthcare resource utilisation. While the CORE-VNS registry was not expressly designed to test hypotheses, subgroup analyses and exploratory analysis that require hypothesis testing will be conducted across propensity score matched treatment groups, where possible based on sampling.

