### Clinical endpoints

Beyond information on demographics, medical history and genetics (where applicable) in the global DRE population, the registry aims to gather a broad range of clinical outcome measures to assess the purported benefits of VNS. The clinical endpoints of the registry include data collection at baseline as well as 3, 6, 12, 24 and 36 months after implant. Long-term follow-up data may continue annually through 60 months after implant where applicable (table 2).

**Table 2 T2:** Protocol-specified visit schedule and assessments for participants in the CORE-VNS registry. After the first year, patients will return to the clinical site for annual visits, where all endpoint measures will be assessed. At unscheduled visits, only VNS parameter settings, concomitant treatment for epilepsy and safety data will be collected

Target follow-up	Baseline	Implant	Follow-up (post implant)					
	−45 to 5 days before implant	0	Titration visit(s)	3 months (±45 days)	6 months (±45 days)	12/24/36 months (±45 days)	Long-term follow-up *Every 12 months until 60 months or study end (±60 days*)*	Unscheduled visits
Informed consent/assent/data privacy	X							
Inclusion/exclusion criteria	X							
Demographics and medical history	X							
VNS Therapy implant/revision/explant		X	*As needed*	*As needed*	*As needed*	*As needed*	*As needed*	*As needed*
VNS Therapy parameter settings		X	X	X	X	X	X	X
Concomitant treatments for epilepsy†	X			X	X	X	X	
Rescue medication use	X			X	X	X	X	
Seizure frequency	X			X	X	X	X	
Maximum seizure-free period	X			X	X	X	X	
Seizure severity/postictal severity	X			X	X	X	X	
Quality of life	X			X	X	X	X	
Quality of sleep (PSQI or CSHQ)‡	X			X	X	X	X	
Healthcare utilisation	X			X	X	X	X	
VNS Therapy feature use (if applicable)			X	X	X	X	X	X
Deaths and AEs related to VNS (if applicable)§		X	X	X	X	X	X	X
Pregnancy reporting form (if applicable)	*As needed*	*As needed*	*As needed*	*As needed*	*As needed*	*As needed*	*As needed*	*As needed*
Device deficiencies (if applicable)		X	X	X	X	X	X	X
Study completion or withdrawal			*At study exit*	*At study exit*	*At study exit*	*At study exit*	*At study exit*	*At study exit*

*During the long-term follow-up phase, subjects will have yearly follow-up visits until 60 months post implant or until study end (whichever comes first).

†Pharmacological and non-pharmacological.

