‡PSQI: Pittsburgh Sleep Quality Index for subjects ≥18 years of age at baseline/CSHQ: Children Sleep Habit Questionnaire for subjects 2–17 years of age at baseline.

§AEs possibly, probably or definitely related to VNS Therapy per investigator assessment (including those with unknown relationship).

AEs, adverse events; CSHQ, Children Sleep Habit Questionnaire; PSQI, Pittsburgh Sleep Quality Index; VNS, vagus nerve stimulation.

Clinical assessments include: average seizure frequency per month for the 3 months prior to each protocol-specified visit and maximum seizure-free period over 90 days prior to each protocol-specified visit. Seizure severity and postictal severity are based on participant-rated categorical outcome (very mild; mild; moderate; severe; and very severe). Quality of life assessment is based on a participant-rated categorical outcome (very good: could hardly be better; pretty good; good and bad parts about equal; pretty bad; or very bad: could hardly be worse). Given the anticipated recruitment and the duration of the study, Likert scales were selected to limit the impact of visit duration on enrolment and participant retention.

On account of previously reported interactions between VNS and sleep apnoea and the limited evidence in this area,^20–22^ quality of sleep assessment was collected through validated scales. Participants who are over 18 years of age at baseline are requested to complete the Pittsburgh Sleep Quality Index (PSQI) at each protocol-specified visit, including baseline.^23^ Participants who are between 2 and 18 years of age at baseline complete the Children’s Sleep Habit Questionnaire.^24–26^ Participants who are less than 2 years of age at baseline are not assessed for sleep quality.

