Principal analysis of the full cohort data will occur at 3 years of follow-up and will be summarised using descriptive statistics for the relevant analysis population (mSAF or FAS). Intermediate analysis will also be conducted for the full cohort at each year after implant, and topics of this analysis are further described in the following section. Continuous variables will be summarised using the number of observations, mean, median, SD, minimum and maximum values. Categorical variables will be summarised using the number of observations and percentages. Absolute scores and changes from baseline with 95% CIs will be reported for each clinical endpoint at each follow-up visit. VNS-related adverse events, including serious adverse events and deaths, will be presented by system organ class and preferred term as total counts and percentages. These adverse events will be further described by their relationship to VNS implant and/or stimulation and the current status (eg, ongoing, resolved, death, chronic or unknown).

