### Ethics and dissemination

The registry is being conducted in accordance with the ethical principles that have their origin in the Declaration of Helsinki, and that are consistent with Good Clinical Practice described in ISO 14155, and the applicable regulatory requirement(s) of each participating clinical centre. Any additional requirements imposed on the study by a clinical centre’s Institutional Review Board or Ethics Committee will be followed.

Beyond the principal analysis of these results described in the previous section, which will focus on our assessment of the primary clinical and safety outcomes in the FAS and mSAF populations, additional exploratory analyses are expected within this database. The CORE-VNS registry will collect a variety of exploratory clinical outcomes that have not been robustly characterised in a large population treated with VNS. These exploratory analyses will constitute a significant portion of the dissemination strategy for this large database. All results will be submitted to peer-reviewed scientific journals and may also presented as abstracts at large epilepsy congresses with international audiences.

For some of the following analyses, descriptive statistics will be sufficient to describe how practice and outcomes vary, but in other cases direct hypothesis testing is warranted. If hypothesis testing is required for these exploratory analyses, propensity scoring based on baseline demographics and clinical histories will be employed to create matched treatment groups for comparison.

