### General demographics and medical history

The CORE-VNS registry is designed to be the largest, prospective, international data set ever collected of people receiving VNS for DRE. This creates an opportunity to assess the global demographic profile of people who receive adjunctive VNS. Regional variances in age, sex, ethnicity, race, aetiology (structural, genetic, infectious, metabolic, immune, unknown), epilepsy syndrome (childhood absence, juvenile absence, juvenile myoclonic, infantile spasms, West, Dravet, Lennox-Gastaut, tuberous sclerosis, continuous spikes/slow waves during sleep, electrical status epilepticus, epilepsia partialis continua, unknown, other), epilepsy type (focal, generalised, combined, unknown), history of brain surgery, family history of seizures, comorbidities, duration since epilepsy diagnosis and medical history of people who proceed to VNS will be investigated. Furthermore, we aim to better understand the prescribing history of failed ASMs in the DRE population.

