### VNS and sleep quality

VNS has been reported to exacerbate and/or induce sleep apnoea in multiple independent case series.^20–22^ Apnoeic events are known to decrease quality of sleep and overall health outcomes. At the same time, uncontrolled epilepsy can impact sleep quality and is associated with increased incidence of obstructive sleep apnoea.^33^ Better understanding of the risk–benefit profile of VNS with respect to quality of sleep and health outcomes seems warranted.

VNS parameters have long been understood to play a role in this adverse effect, and VNS-induced apnoea can be managed by reducing the intensity of stimulation.^34^ Day/night programming was developed in part to help ameliorate apnoeic events through changes in programming parameters during sleep, but the implementation of this technology for reducing incidence of VNS-induced apnoea has not been examined. Therefore, whether day/night programming can improve sleep quality will be investigated. In adult patients, this analysis will be limited to participants with sufficient cognitive ability to provide a complete PSQI as the tool is not validated for use by caregivers.

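### The stated basis for propensity matching does not name the baseline value of the outcome being compared, although the registry collects it

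*Protocol article*

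**What the plan says.** The main text, under Ethics and dissemination, separates two kinds of exploratory analysis. For some, "descriptive statistics will be sufficient to describe how practice and outcomes vary, but in other cases direct hypothesis testing is warranted". Where testing is needed, "propensity scoring based on baseline demographics and clinical histories will be employed to create matched treatment groups for comparison". The abstract gives the same approach with a qualifier: "hypothesis testing will be conducted across propensity score matched treatment groups, where possible based on sampling".

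The outcomes are measured before implant. Seizure frequency is recorded as "average seizure frequency per month for the 3 months prior to each protocol-specified visit", and the baseline visit is one of those visits. Table 2 also marks baseline for seizure severity, quality of life, sleep quality and healthcare utilisation. These rows are separate from the row "Demographics and medical history". The section on general demographics and medical history lists age, aetiology, syndrome, prior brain surgery and similar items, and says that "comorbidities, duration since epilepsy diagnosis and medical history of people who proceed to VNS will be investigated". It lists no baseline outcome score.

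Under Statistical analysis, the descriptive principal analysis states: "Absolute scores and changes from baseline with 95% CIs will be reported for each clinical endpoint at each follow-up visit". No outcome scale is stated for the matched tests.

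**The concern.** In a non-randomised comparison of devices, features or concomitant therapies, the pre-treatment value of the outcome is usually among the strongest predictors of the later value. It may also influence who gets which option. Matching on age, aetiology and history need not balance a sleep or quality-of-life score.

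Sleep is the plainest case. The article says "Day/night programming was developed in part to help ameliorate apnoeic events through changes in programming parameters during sleep" and then plans to ask whether that feature improves sleep quality. If clinicians choose it partly for people who already sleep badly, its users start with worse scores and would tend to improve more through regression to the mean. A difference could then appear without any effect, or a real one could be hidden. Even with balanced groups, leaving out the baseline value gives up precision, in analyses that the article says were not designed with adequate power.

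**Working it through.** **Reproduction.** The article gives no power, alpha, SD, correlation or expected imbalance, so there is no figure to reproduce. What follows is an illustration.

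**Assumed inputs.** Outcome SD of 1 at baseline and follow-up. Correlation rho between them of 0.3 to 0.8. Residual baseline difference d after matching of 0.1 or 0.3 SD. 100 per matched group. Two-sided 5% test. No true effect when computing error rates. Follow-up depends linearly on the measured baseline, and groups are selected on that measured value.

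**Bias of an unadjusted change score.** The expected difference in change under no effect is −(1 − rho) × d.

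**Type I error.** SE = √[2(1 − rho)] × √(2/100). With z = (1 − rho)d / SE, the error is Φ(−1.96 + z) + Φ(−1.96 − z). For rho = 0.5 and d = 0.3: the bias has size 0.15, SE = 1 × 0.1414, z = 1.06, and the error is 18.5%.

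**Precision.** The variance factor is 2(1 − rho) for the change score and 1 − rho² with baseline as covariate (ANCOVA). Their ratio is (1 + rho)/2, so the required sample size falls by (1 − rho)/2. The power columns are for a true effect of 0.3 SD with balanced groups.

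| rho | Size of bias, d = 0.1 / 0.3 (SD) | Type I error, d = 0.1 / 0.3 | Reduction in N with adjustment | Power, change score | Power, adjusted |
|---|---|---|---|---|---|
| 0.3 | 0.07 / 0.21 | 7.0% / 24.1% | 35% | 43% | 60% |
| 0.5 | 0.05 / 0.15 | 6.4% / 18.5% | 25% | 56% | 69% |
| 0.7 | 0.03 / 0.09 | 5.9% / 13.0% | 15% | 78% | 84% |
| 0.8 | 0.02 / 0.06 | 5.6% / 10.3% | 10% | 92% | 94% |

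**Simulation check.** With rho = 0.5, d = 0.3, 100 per group and 4000 runs, the mean estimate was −0.152 SD for the change score and −0.002 SD with adjustment.

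**If the test used the raw follow-up value instead.** Under the same model the bias is rho × d. At d = 0.3 and rho = 0.5 that is 0.5 × 0.3 = 0.15 SD. A residual imbalance therefore matters on either unadjusted scale.

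**The case against.** The strongest reply is that this reads too much into one phrase of a condensed article. The article refers to a statistical analysis plan that is not shown, and the full covariate list may be there. Clinical history is not defined. Baseline seizure frequency looks back over 3 months, and baseline rescue use and healthcare utilisation over 12 months, so these could fairly count as history. Nothing in the article excludes them. This stands, and it is why the point is firmest for sleep and quality-of-life ratings. It does not remove the point: the article states a basis for the score, and its own table keeps outcome measures apart from demographics and history.

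Four stronger readings are tempting and are not supported.

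- *Every hypothesis test is affected.* The abstract limits matching to where it is possible. The titration section plans a generalised linear mixed model and a Cox model that are not described as matched. VNS-related adverse events and visits needed for titration have no pre-implant value.
- *The matched tests compare unadjusted changes.* Changes from baseline are stated, beside absolute scores, for the descriptive analysis only. A change-score test is an assumption of the illustration.
- *Users of day/night programming are known to start with worse sleep.* The article also speaks of apnoea induced by VNS, which arises after implant. Choosing the feature for that reason would not be selection on the pre-implant score.
- *Adjustment is always the better analysis.* If groups differ by a stable trait, so that both means are shifted by d, the change score is unbiased and ANCOVA is off by d − rho × d = (1 − rho)d. The documents do not show which case applies, so both results should be shown.

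**Conclusion.** The point holds in a limited, conditional form. For exploratory comparisons tested in matched groups, the stated propensity basis does not name a collected variable that is likely to predict the outcome. Whether harm follows depends on three things that the article does not settle: whether the value is in fact left out, whether groups still differ on it after matching, and which outcome scale is tested.

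Under the assumptions above, the inflation is slight at 0.1 SD (5.6% to 7.0%) and material at 0.3 SD (10.3% to 24.1%). The loss of precision relative to a change-score test needs no imbalance and equals 10% to 35% of the required sample size. A reader might infer that the registry's main results are biased. They are not touched by this point, because the principal analysis is descriptive and compares no groups. This is an inexpensive improvement to a stated method, not a demonstrated error.

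**What to change.** In the Ethics and dissemination section, after the sentence on propensity scoring, state that where the compared outcome has a pre-implant value:

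1. that value enters the propensity model (seizure frequency on a log scale, the PSQI or CSHQ score, the severity or quality-of-life category, or prior utilisation, as applicable);
2. its balance after matching is checked and reported;
3. it is a covariate in the matched-sample analysis (ANCOVA, or the ordinal or count equivalent);
4. the comparison of change from baseline is shown alongside as a sensitivity analysis.

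If the analysis plan already does this, a statement to that effect is enough. No new data are needed. The cost is a few lost pairs from matching on one more variable, and the loss of participants without a baseline score from that comparison.

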### Participant eligibility and enrolment

Participants considered eligible for enrolment in CORE-VNS must meet the following criteria:

Clinical diagnosis of DRE to be treated with VNS Therapy. People receiving either initial implants or replacement implants are eligible for enrolment.Able and willing to comply with the frequency of protocol-specified visits.Able to voluntarily provide informed consent, by participant or their legal guardian in accordance with institutional policies. In some cases, individuals who are less than 18 years of age may be required to sign an assent affirming their agreement to participate.

There are no specific exclusion criteria for this all-comers registry. Further, local regulatory approvals may limit access to specific VNS Therapy devices for some patient populations.

Participants are considered enrolled on completion of the baseline visit (which includes affirmation of informed consent) and successful implantation of the VNS Therapy system.

There will be no deviation from standard clinical care and only those people who the clinical team decides are suitable for VNS implantation/replacement will be offered the choice to participate. There will be no change to clinical care based on whether an individual chooses to participate or not. Participants may elect to exit the registry at any time without the need to give a reason and with no adverse impact on their clinical care. Participants who are discontinued by the investigators will have reasons documented for discontinuation (eg, early termination or lost to follow-up). Data from participants who withdraw or are withdrawn from the registry will be included to the point of withdrawal.

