### Statistical analysis

Given the exploratory nature of the data set and the principal aim to provide preliminary information on clinical outcome and safety data, the sample size is not calculated based on a statistical power. There are no prospective requirements for enrolment at each centre, meaning that certain centres may contribute a much larger percentage of the study population than others.

Three analysis populations are prospectively defined: modified enrolled population (mENR), modified safety population (mSAF) and the full analysis set (FAS). The mENR or ‘screened’ population are participants with a signed and dated informed consent who meet all registry requirements, consistent with ISO-14155:2011. The mSAF population is defined as all participants in the mENR population who underwent an implantation procedure with the VNS Therapy system, whether that procedure was successful or not. The FAS population includes all participants in the mSAF population with at least one post-baseline efficacy (clinical or performance) assessment. The FAS will be used for efficacy and performance summaries, including all subpopulation analyses. All safety analyses and subject disposition summary will be assessed using the mSAF population.

Further subpopulation analysis will occur in the following groups, provided they include more than 1% of the total subject count:

Age class (paediatric <18 years of age or adult ≥18 years of age).Implant type (new implant or replacement implant).Implant timing (Early: ≤4 ASMs failed or <5 years since initial epilepsy diagnosis at time of implant or Late: All other patients).Seizure type/focus (generalised, focal, combined or unknown).Specific epilepsy syndrome (if known).Epilepsy aetiology (if known).VNS Therapy system model.­ Non-responsive VNS Therapy device: Pulse (Model 102), Pulse Duo (Model 102R), Demi-Pulse (Model 103), Demi-Pulse Duo (Model 104), AspireHC (Model 105).­ AspireSR (Model 106).­ SenTiva (Model 1000).Feature use (AutoStim ON vs OFF; day/night ON vs OFF; scheduled programming ON vs OFF).

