### Regional practice and feature use

This registry aims to better understand regional differences in the implementation of VNS. Specifically, there is interest in identifying regional variances in clinical and safety outcomes associated with different implementations of VNS dosing and standard clinical practice. Newer models of VNS devices have only recently become available in some of the regions participating in the registry, so differences may be apparent in the use of new features. The features available in these newer models offer more programming flexibility and the potential for improved clinical and safety outcomes, but may also add complexity to the therapy. In this study, rationale for the selection of a Model 1000 ‘SenTiva’ generator is collected by ranking the relative importance of each feature in the eventual decision. The rationale options for device or feature selection include: scheduled programming, day/night programming, low heart rate detection, prone position detection, events and trends, availability of AutoStim with a smaller generator.

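### Feature ON versus OFF contrasts are not restricted to capable devices, and the stated matching basis leaves out device model, place, implant date and later switching

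*Protocol article*

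**What the plan says.** The Statistical analysis section lists, among the subpopulation factors, "Feature use (AutoStim ON vs OFF; day/night ON vs OFF; scheduled programming ON vs OFF". It fixes the population: "The FAS will be used for efficacy and performance summaries, including all subpopulation analyses". Safety is handled separately: "All safety analyses and subject disposition summary will be assessed using the mSAF population". The only entry condition for a subgroup is a size rule, "provided they include more than 1% of the total subject count". OFF is not defined, and no contrast is tied to particular generators.

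The method for any test in the exploratory analyses is given under Ethics and dissemination: "propensity scoring based on baseline demographics and clinical histories will be employed to create matched treatment groups for comparison". Matching applies only if a test is needed and, according to the Abstract, only where sampling allows.

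On access to devices, the eligibility section says that "local regulatory approvals may limit access to specific VNS Therapy devices for some patient populations", and the section on regional practice says that "Newer models of VNS devices have only recently become available in some of the regions participating in the registry". Table 1 shows Demi-Pulse with none of the features, AspireSR (Model 106) with AutoStim alone, and SenTiva (Model 1000) with all of them. In Table 2, feature use is first recorded at titration visits, not at baseline or implant, and then at every later visit.

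**The concern.** A propensity score balances the factors that go into it. Here the main determinants of whether a feature is ON include which generator was implanted, where and when. None of these is a patient demographic or an item of clinical history in the ordinary sense. If they also relate to outcome, groups matched on the stated basis can differ for reasons unrelated to the feature and still be presented as matched.

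Timing is a second problem. Feature status is set after implant and may change. The section on sleep quality says day/night programming was developed partly to lessen apnoeic events, and then asks whether it improves sleep. If clinicians turn it on because sleep has worsened, a score built at baseline cannot balance that decision, and a real benefit could be masked or reversed.

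This matters because the article asks effect questions of these features: whether scheduled programming cuts office visits for titration, and whether day/night programming improves sleep. It also expects the registry to inform physicians, regulators and payers.

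**Working it through.** The plan gives no power, alpha or effect figure to reproduce. The check has three parts: a comparison of the text, the make-up of the OFF group, and a simulation. The last two use assumed values.

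**1. What drives feature exposure, and whether the stated basis covers it**

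| Factor | Where the article shows it matters | Named in the matching basis? |
|---|---|---|
| Device model | Table 1 | No |
| Country or region | Eligibility section; Regional practice and feature use | No |
| Centre practice | Design limitations (titration and programming vary by centre and region) | No |
| Implant date | Regional practice (recent arrival of newer models); Design limitations (scheduled-programming users perhaps less affected by COVID-19 delays) | No |
| Problems arising after implant | VNS and sleep quality; Table 2 | No; not knowable at baseline |

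Design limitations also says that regional differences in practice may confound outcomes. So place can act on both exposure and outcome. The safeguard offered there concerns regional analyses, and the possible enrolment-year subgroup is not linked to the feature contrasts.

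**2. Who is in OFF, read literally**

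Let s be the share of participants with a capable generator and f the share of those with the feature ON. Neither is given, so both are assumed. With N participants, OFF holds N(1 − s·f), of whom N(1 − s) could not have had the feature ON:

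incapable share of OFF = (1 − s) / (1 − s·f)

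- s = 0.9, f = 0.2: 0.1 / 0.82 = 12%
- s = 0.5, f = 0.5: 0.5 / 0.75 = 67%
- s = 0.3, f = 0.8: 0.7 / 0.76 = 92%

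Suppose capable and incapable groups differ by 10 points for unrelated reasons. The spurious ON minus OFF difference is then 10 times this share, or 1.2 to 9.2 points.

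**3. Simulation with no true feature effect**

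Inputs: N = 823 (Study status). All else is assumed:
- two equal regions, with capable devices in 85% and 35% of participants;
- feature use among capable devices centred on 40%, with log-odds 0.5 higher in one region and 0.5 lower in the other;
- response centred on 50%, with a weak dependence on a baseline covariate that also affects feature use;
- 1:1 caliper matching, two-sided 5% test, 600 runs.

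| Regional response gap | Whole cohort, baseline covariates only: mean difference; type I error | Capable devices only, region in score and matched exactly: mean difference; type I error |
|---|---|---|
| 0 points | 0.0; 5.3% | 0.0; 5.8% |
| 10 points | 4.4; 14.3% | 0.4; 6.7% |
| 20 points | 8.9; 49.8% | 0.0; 6.0% |

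Matched pairs fall from about 224 to about 184. The simulation error of a 5% rate is √(0.05 × 0.95 / 600) = 0.9 points, so the right-hand column is compatible with 5%.

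Hand check, ignoring the patient covariates:
- Odds of ON among capable devices are (0.4/0.6)·e^0.5 = 1.099 and (0.4/0.6)·e^−0.5 = 0.404, so the probabilities are 0.524 and 0.288.
- ON overall by region: 0.85 × 0.524 = 0.445 and 0.35 × 0.288 = 0.101.
- The first region makes up 0.445/0.546 = 82% of ON and 0.555/1.454 = 38% of OFF, a gap of about 0.43.
- Multiplied by 10 and 20 points this gives about 4.3 and 8.7, in line with the simulated 4.4 and 8.9.

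**The case against.** The strongest reply is that this is a condensed article. It refers to a statistical analysis plan that is not shown, and the full covariate list, exact-match factors and timing of exposure could stand there. Several stronger readings are tempting, and the article does not support them.

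- *The score uses only demographics and clinical history.* The article names that basis but does not call it a closed list. What stands is that the stated basis, followed as written, omits the factors above.
- *Participants without the feature are counted as OFF.* This is a literal reading of an undefined term. Feature use is collected where it applies, and device model is a separate subgroup factor, so restriction may be intended. The FAS also governs efficacy summaries, not safety.
- *The contrasts are confounded.* They are open to confounding. With no regional gap the simulation shows no bias. Some baseline items, such as ethnicity or aetiology, may vary by region, so matching on them could remove part of any regional effect.
- *These are the registry's main tests.* The principal analysis is descriptive, testing is conditional, and the article says the registry was not designed to power the exploratory analyses.
- *The bias is 12 points.* Regions with 60% and 40% response and 80% and 20% feature use give 0.8 × 0.6 + 0.2 × 0.4 = 56% against 0.2 × 0.6 + 0.8 × 0.4 = 44%. None of these inputs is in the article.
- *The intervals are too narrow because centre is ignored.* The article does say that "certain centres may contribute a much larger percentage of the study population than others", but it states no variance method, so silence proves nothing. The usual design effect also suits cohort-level means better than contrasts that vary within a centre.

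The article does acknowledge regional practice and COVID-19 timing, and it plans a mixed model for programming settings. These are partial mitigations, and none is tied to the feature contrasts.

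**Conclusion.** The point holds as a weakness in what the article fixes. The matching basis it states does not fit the feature contrasts it lists, on its own account of who gets which device, where and when. OFF needs a definition, and exposure that begins after implant needs a rule. If the method were followed as written, these exploratory comparisons would be open to confounding.

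The size is unknown. The spurious differences of about 0, 4 and 9 points rest on assumed regional gaps, device shares and feature use, and on counting incapable devices as OFF. They show direction and plausible scale, not an estimate for this registry. Bias from later switching was not quantified. The descriptive principal analysis is not affected.

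**What to change.** - **Restrict by device.** Limit AutoStim contrasts to Models 106 and 1000, and day/night and scheduled programming contrasts to Model 1000. Define OFF as available but not in use. Apply the same rule in the mSAF if safety is compared by feature.
- **Match on place and time.** Add country or centre and implant year to the score, or match within country, and exclude countries with no overlap between ON and OFF. On average there are 823/61 = 13.5 participants per centre and 823/15 = 54.9 per country, so country will often be the workable level.
- **Fix the exposure time.** Classify by feature status at a fixed early landmark and count outcomes afterwards, or treat use as time-varying with inverse-probability weights. With a landmark, include problems recorded before it among the covariates. For titration visit counts, the landmark must precede the visits being counted.

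This takes wording and programming, on data the registry already collects. The price is fewer matched participants and wider intervals: in the simulation about 184 pairs instead of 224, a loss of 40/224 = 18%. If the analysis plan already contains these rules, a sentence in each report of a feature contrast would be enough.
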